### Circadian Rhythm Measurements

The circadian rhythm is expected to be affected by the feeding strategy. Electroencephalography, electrooculography, and electromyography will be recorded for 24 hours on admission, day 3, day 7, and day 14 (with a margin of 1 day) or before discharge if the discharge is before day 14. Multichannel registration will be performed using a standard device (Brain RT, OSG or Morpheus, Micromed SpA). Melatonin and cortisol will be measured in the study blood samples, as melatonin and cortisol both have a clear relationship with circadian rhythms [28,29]. The blood samples used for gene expression analysis may be used to determine the internal time of peripheral blood mononuclear cells [30]. The difference between this internal time and the time of blood draw is a measure of circadian disturbances. In addition to the blood samples, salivary melatonin and cortisol levels will be measured to evaluate the possibility of measuring the circadian rhythm in saliva [31]. As ambient light and sound may affect and thus confound circadian rhythm [32,33], quantitative light and sound measurements will be taken at the bedside during ICU stay. All routinely monitored vital signs (including heart rate, respiratory rate, oxygen saturation, perfusion index, body temperature, central venous pressure, end-tidal carbon dioxide, arterial blood pressure, oxygen saturation, and electrocardiogram waveforms) will be stored at 1 Hz to 200 Hz intervals for further analysis.

### Data Handling and Record-Keeping

Data will be collected electronically in a pseudonymized electronic case record form (eCRF) with an audit trail unambiguously linked to the source file using the *OpenClinica* clinical data management system (OpenClinica Community; version 3.12.2; OpenClinica LLC). Every day, the types and amounts of EN and PN delivered will be registered in the eCRF. Interruptions in EN delivery and gastrointestinal intolerance will be registered daily. The duration (in minutes) and the cause of interruption of EN delivery will be recorded. The data will be manually transferred into and checked for accuracy in the eCRF by the research team. Extensive range and consistency checks will be performed by the monitor of the study. All systemically administered medications, analyses of routine clinical chemistry, and whole blood glucose levels during the stay in PICU will be registered in the electronic patient file to be retrieved after completion of the study. The vital status at 30 days (and at later follow-up times) will be recorded for all patients in consultation with the National Personal Records Database. When this information is not available, the vital status will be checked through the hospital information system or regional network of pediatricians and general practitioners. All original records, such as consent forms, case report forms, and relevant correspondence, will be archived according to national regulations.

### Outcome Measures

#### Primary End Points

The primary outcome of this study will be the feasibility of a daily feeding and fasting cycle (*intermittent feeding* strategy) compared with a continuous 24 hours per day feeding strategy in critically ill children. The primary outcome is defined as the difference in ketosis (3-β-hydroxybutyrate levels) between the groups under the condition of noninferiority regarding caloric intake. The amount of nutritional intake is defined as the daily caloric intake as a percentage of the estimated REE based on the body weight–based or body weight and length–based Schofield equation.

#### Secondary End Points

Secondary end points will comprise outcomes regarding the safety, feasibility, and efficacy of the intervention. The primary safety outcome is defined as the difference in the incidence of severe and resistant hypoglycemic events and severe gastrointestinal complications between the groups. For definitions of severe and resistant hypoglycemia and severe gastrointestinal complications, see the *Discontinuation of the Study Intervention* section*.*

The secondary safety outcomes comprise the following:

Overall blood glucose control (hypoglycemic incidents and hyperglycemic incidents)Complications of nutritional supportHyperlactatemia during the feeding interval

As patients with a feeding and fasting cycle in the *intermittent* group may be considered at increased risk for hypoglycemia during the fasting interval, we will also report hypoglycemic incidents (glucose <2.2 mmol/L) during the time window of the randomized intervention for both groups as the number of nights with at least one episode of hypoglycemia divided by the total number of days of the intervention. As patients in the *intermittent* group may be considered at increased risk for hyperglycemia during the condensed feeding period, we will report the hyperglycemic incidents (glucose >10 mmol/L) during the time window of the randomized intervention for both groups as the number of days with at least one episode of hyperglycemia divided by the total days of the intervention.

Possible complications of nutritional support are shown in Textbox 1.

Hyperlactatemia is defined as an increase in arterial lactate levels above 2 mmol/L during the feeding interval.

Other secondary outcomes will be feeding intolerance and metabolic (eg, course of ketones, lactate, and free fatty acids) and endocrine responses (eg, insulin and glucagon). Enteral feeding intolerance is defined according to the definition by Eveleens et al [34] (Multimedia Appendix 1). Furthermore, we will evaluate any observed effects of the intermittent feeding strategy compared with continuous nutrition on nutritional intake, circadian rhythm, and clinically relevant outcome measures.

The effects on nutritional intake and circadian rhythm that will be investigated are presented in Textbox 2.

Clinically relevant outcome measures will be collected until 30 days after admission and are presented in Textbox 3.

Possible complications of nutritional support.

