### Per-Protocol Stop of Study

A switch to oral intake will be made as soon as it is deemed safe by the clinician responsible for the patient.

The study intervention will last until admission day 14, until the child could be fed by mouth (oral feeding), or until discharge from the PICU, whichever comes first. After day 14, the intervention will stop, and nutritional support will be provided according to standing orders when oral intake remains insufficient.

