### Discontinuation of the Study Intervention

We defined a stopping rule (no-go) for individual patients to be withdrawn from the study who develop the following:

Hypoglycemia (<2.6 mmol/L) with clinical symptoms (eg, pallor, transpiration, irritability, lethargy, loss of consciousness, and convulsions) or severe hypoglycemia (<2.2 mmol/L) *and* who are resistant to parenteral glucose administration; *resistance* is defined as no elevation of glucose within 1 hour after parenteral glucose bolus (1 mL/kg glucose 10%) administration and elevation (double) of standard glucose infusion via the standard local protocolAcute, nonocclusive mesenteric ischemia (ie, intestinal perforation and necrotizing enterocolitis) not attributed to an anatomical substrate (eg, volvulus)

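### The only rate defined for hypoglycemic incidents divides nights by days and omits daytime episodes, so it measures the fasting window and cannot by itself describe overall glucose control

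*Protocol article*

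**What the plan says.** Secondary End Points in the protocol article names "Overall blood glucose control (hypoglycemic incidents and hyperglycemic incidents") among the secondary safety outcomes. It then explains that the intermittent group "may be considered at increased risk for hypoglycemia during the fasting interval", and continues: "we will also report hypoglycemic incidents (glucose <2.2 mmol/L) during the time window of the randomized intervention for both groups". The rate given for these incidents is the "number of nights with at least one episode of hypoglycemia divided by the total number of days of the intervention". The next sentence gives the hyperglycemia rate as the "number of days with at least one episode of hyperglycemia divided by the total days of the intervention".

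Hypoglycemia appears in one other defined outcome, the primary safety outcome, which is the "difference in the incidence of severe and resistant hypoglycemic events and severe gastrointestinal complications between the groups". For its definitions the article refers to Discontinuation of the Study Intervention, where an episode qualifies only in patients "who are resistant to parenteral glucose administration". That outcome is not limited to any time of day.

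The intervention runs to admission day 14, or "until the child could be fed by mouth (oral feeding), or until discharge from the PICU, whichever comes first" (Per-Protocol Stop of Study). The text does not say how intervention days are counted, or which hours make a night for a continuously fed child.

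**The concern.** Two features of the definition need attention.

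- **Units.** The numerator rises by at most one per night, while the denominator counts days. The hyperglycemia rate uses the same unit above and below, so the two halves of one outcome are built differently. If the number of nights in a course is not equal to the number of days, a child with an episode every night does not score 1, and the shortfall depends on length of stay.
- **Coverage.** A rate that counts only nights cannot register a daytime episode. The heading it sits under is overall glucose control, and the primary safety outcome takes in only episodes that resist treatment. A daytime value <2.2 mmol/L that corrects with glucose therefore falls between the two definitions.

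At stake is whether the safety report can support a statement about hypoglycemia over the full 24 hours. Safety and glycemic control are part of the trial's stated hypothesis (Discussion, Hypothesis), and the ethics board's safety request concerned the risk of hypoglycemia (Blood Glucose Management).

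**Working it through.** The article states no expected rate, power or precision for this outcome, so there is no figure to reproduce. The check is arithmetic on the definition.

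**Inputs from the article**
- Rate: nights with an episode / days of intervention (Secondary End Points).
- Maximum course: to admission day 14 (Per-Protocol Stop of Study). Expected stay at entry: more than 48 hours (Inclusion Criteria).
- Overnight window: 8 hours in neonates, 10 in infants, 12 in children (Intervention Group).
- Glucose is measured at least once daily in the feeding period (Blood Glucose Management), so daytime episodes can be observed.

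**Step 1: ceiling of the rate.** Assume calendar-day counting, with k days holding k-1 nights. The ceiling is (k-1)/k and the relative understatement is 1/k.

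| k (days) | Ceiling | Understatement |
|---|---|---|
| 2 | 0.50 | 50% |
| 3 | 0.67 | 33% |
| 5 | 0.80 | 20% |
| 7 | 0.86 | 14% |
| 10 | 0.90 | 10% |
| 14 | 0.93 | 7% |

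Now assume 24-hour days instead. Each full day holds one night, so the ceiling is 1.00 at every length. A 48-hour stay from noon to noon shows the difference: it touches 3 calendar days and holds 2 nights, which gives 2/3 on the calendar count and 2/2 on the 24-hour count.

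**Step 2: effect on the arm comparison.** Under calendar counting with equal per-night risk, the ratio of the two arms' rates is [(a-1)/a] / [(b-1)/b] for courses of a and b days.
- Equal lengths (4 and 4): 0.75/0.75 = 1.00, no distortion.
- 3 and 5 days: 0.667/0.80 = 0.83.
- 3 and 7 days: 0.667/0.857 = 0.78.
- 5 and 7 days: 0.80/0.857 = 0.93.

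These length pairs are illustrations. The article gives no figure for intervention duration by arm.

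**Step 3: daytime coverage.** If night means the overnight window, the hours outside the numerator are 24-8 = 16 (neonates), 24-10 = 14 (infants) and 24-12 = 12 (children). If a share s of affected days has daytime episodes only, the rate captures 1-s of affected days before any denominator effect. For assumed s of 10%, 25% and 50%, that is 90%, 75% and 50%. The article gives no value for s in either arm.

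**Step 4: where a daytime episode is counted.**

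| Daytime glucose <2.2 mmol/L | Night rate | Primary safety outcome |
|---|---|---|
| Resistant to parenteral glucose | No | Yes |
| Responds to treatment | No | No |

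The second row is the gap.

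**The case against.** The best defense is that the night focus is deliberate. The article gives its reason, and the word also presents the rate as an additional, targeted measure. Overall glucose control is listed without any restriction to nights. Resistant daytime episodes still count in the primary safety outcome. Blood glucose values during the PICU stay are registered for retrieval (Data Handling and Record-Keeping), so a 24-hour summary remains possible. The analysis plan for secondary outcomes is to be published separately, and day-counting rules commonly sit there.

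Most of this stands. It shows that the rate is sensible as a fasting-window measure and that nothing is lost from the data. It does not close the gap. The numerator and denominator are stated in the article, not deferred, and no other rate is defined for hypoglycemic incidents that respond to treatment.

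Two stronger readings are tempting, and the article supports neither.

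- **That the rate is biased downward, most of all in short stays.** This follows only from calendar-day counting. Under 24-hour counting it disappears, and the article does not say which applies. Even on the calendar reading, the factor is the same in both arms when durations are equal.
- **That omitting daytime episodes removes more events from the control arm and so makes the between-arm difference wrong.** This needs control episodes to be spread evenly over the day, which nothing in the article supports. Other features could shift the balance. In the intermittent arm only, insulin is stopped 1 hour before the overnight interruption, and neonates and infants in that arm receive a glucose infusion overnight (Blood Glucose Management). Glucose is also measured more often overnight in that arm (Study Blood Samples), which affects detection.

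**Conclusion.** The point holds in a limited form and is minor. As written, the only rate defined for hypoglycemic incidents has mismatched units and, read literally, leaves out daytime episodes that respond to treatment. It can describe hypoglycemia in the fasting window. It cannot by itself describe overall glucose control.

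The size of the unit problem depends on an unstated convention. It is nil with 24-hour days. With calendar days holding one fewer night, the ceiling runs from 0.67 at 3 days to 0.93 at 14. The arm comparison is affected only if, in addition, durations differ between arms. Neither the direction nor the size of any between-arm bias from omitted daytime episodes can be determined from the article, so no claim about which arm is favored is warranted.

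**What to change.** Replace the single hypoglycemia rate with two, both at the existing reporting threshold of <2.2 mmol/L:

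1. **Overall measure:** intervention days with at least one value below the threshold at any hour, divided by intervention days. This matches the hyperglycemia rate.
2. **Fasting-window measure:** nights with at least one such value, divided by nights of intervention.

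Define night by the same age-specific clock window in both arms. State how intervention days are counted, and include a partial first or last day in the night denominator only if it contains night time.

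The cost is one extra derived rate and a few lines of definition. Glucose values during the PICU stay are already recorded, so no new data, samples or change in care are needed.

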### Intervention Group: Intermittent Nutrition

For patients randomized to the *intermittent* nutrition group (intervention group), all nutritional support will be provided during the day and withheld during the overnight feeding interruption period. The overnight feeding interruption period will be designed in an age-dependent manner. The feeding interruption period will be from 2 AM to 10 AM in neonates (≤44 weeks PMA), from 12 AM until 10 AM in infants (<1 year), and from 10 PM to 10 AM in children (≥1 year), as shown in Figure 2. The daily planned nutritional intake will be provided during the condensed feeding period over the day. The starting time of nutritional intake is set to 10 AM to facilitate procedures that require fasting to be performed in the morning. PN (beyond day 7, if necessary) will be provided during the daily age-dependent feeding periods and tapered over 1 hour during the starting and stopping of PN to reduce the risk of swift metabolic shifts (Figure 2) [25,26].

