### Control Group: Continuous Nutrition

Patients randomized to the *continuous* nutrition strategy (control group) will receive nutrition according to current management for 24 hours a day, with a maximum planned interruption period of 2 hours (Figure 2). Planned feeding interruptions exclude interruptions because of clinical ICU care (eg, interventions such as intubation and surgical procedures). Feeding interruptions, timing, and reason will be recorded in the database. PN (beyond day 7, if necessary) will be provided continuously for 24 hours a day without interruption (Figure 2).

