### Study Blood Samples

For all patients, daily plasma glucose levels will be measured and analyzed at the bedside using a blood gas analyzer (ABL90 FLEX PLUS, Radiometer) or point of care meter (Accu-Chek Inform II, Roche Diabetes Care), and daily ketone levels (3-β-hydroxybutyrate) will be measured using the StatStrip Glucose/Ketone meter (Nova Biomedical). In the *intermittent* feeding group, glucose and ketone levels will be measured more frequently during the feeding interruption period (Figure 2).

Additional blood samples for other analyses of metabolism (eg, glucagon, insulin, and free fatty acids) and circadian rhythm (eg, gene expression and cortisol and melatonin) will be taken upon ICU admission and on days 3, 7, and 14 (Figure 2). The blood samples for metabolism will be collected using serum-separating tubes in both fasted (before 10 AM) and fed states (before 10 PM, 12 AM, or 2 AM, depending on the age group) for the intervention group or at similar time points for the continuous group. The blood samples for circadian rhythm will be collected in EDTA tubes every 4 hours during a 24-hour period (a total of 7 samples per 24 hours). The blood samples for gene expression will be collected in *PAXgene* RNA tubes (PreAnalytiX) once daily on the selected days at 10 AM. These additional blood samples will be taken from lines placed for clinical purposes or in combination with draws requested for clinical purposes. Owing to ethical considerations, the number of blood samples will be calculated using the body weight of the individual patient to ensure a maximum of 5% of blood volume for the entire study.

After collection, the blood samples will be immediately stored in a refrigerator. Within 24 hours after collection, the blood samples from serum-separating tubes and EDTA tubes will be centrifuged at 20 °C, and serum or plasma will then be separated and stored at −80 °C for future measurements. The *PAXgene* tubes will not be centrifuged and will be first stored at −20 °C for 1 day before storage at −80 °C to prevent breakage of the tubes. In addition, plasma phosphate, magnesium, and potassium levels will be determined in residuals of clinical plasma samples by the clinical chemical laboratory on days 0 to 4, 7 to 10, and 14.

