#### Primary Outcomes

To assess a significant difference in ketosis between the 2 arms, a 2-tailed *t* test will be performed on the patient means of the highest ketone levels in each fasting period (or similar time point in the control group). A linear mixed model will be used to assess the noninferiority of caloric intake (repeatedly measured over time) in the intervention group, with a noninferiority margin of 33%.

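### Hyperlactatemia is counted only in the feeding interval, with no matched control window; read literally, the counting window depends on allocation and favours the intervention

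*Protocol article*

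**What the plan says.** Under Secondary End Points, the protocol article lists hyperlactatemia among the secondary safety outcomes and defines it: "Hyperlactatemia is defined as an increase in arterial lactate levels above 2 mmol/L during the feeding interval".

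The length of that interval follows from the feeding schedules:

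- **Intervention** (section Intervention Group: Intermittent Nutrition): for the two youngest groups feeding stops "from 2 AM to 10 AM in neonates (≤44 weeks PMA), from 12 AM until 10 AM in infants (<1 year"). The oldest group has the longest nightly stop, 12 h: "from 10 PM to 10 AM in children (≥1 year").
- **Control** (section Control Group: Continuous Nutrition): patients receive "nutrition according to current management for 24 hours a day, with a maximum planned interruption period of 2 hours".

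For other measurements the article says how controls are aligned. The primary ketone test uses the "patient means of the highest ketone levels in each fasting period (or similar time point in the control group"). Under Study Blood Samples, metabolism samples are drawn in the fasted and fed states in the intervention arm "or at similar time points for the continuous group". Hyperglycemia, which the article also links to condensed feeding, is reported for both groups "as the number of days with at least one episode of hyperglycemia divided by the total days of the intervention", without restriction to feeding hours.

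For hyperlactatemia the article gives a threshold and a feeding state. It gives no control clock window, no counting unit and no denominator.

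**The concern.** Daily feeding time is what the trial randomizes. A safety event that can count only during feeding therefore has a counting window set by allocation. Read literally, a lactate above 2 mmol/L at 4 AM counts in a control patient, and the same value at 4 AM does not count in an intervention patient of any age group.

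Restricting the outcome to feeding hours makes sense as a way to look for harm from giving the day's nutrition in fewer hours. Without a matched control window, however, the arm in which harm is suspected is the one with less time to show it. Any resulting bias favours the intervention on a safety outcome.

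**Working it through.** The article states no event rate, power or sample size for hyperlactatemia, so there is no figure of its own to reproduce. The check uses only the feeding schedules, plus an assumed daily risk where marked.

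**Step 1: hours in which an event can count.** Intervention feeding hours are 24 minus the fasting period: 24 − 8 = 16 (neonates), 24 − 10 = 14 (infants), 24 − 12 = 12 (children). Control hours are 24, or 24 − 2 = 22 if the whole planned interruption is used.

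**Step 2: ratio of control to intervention hours.**

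| Age group | Intervention hours | Ratio, 24 h control | Ratio, 22 h control |
|---|---|---|---|
| Neonates | 16 | 24/16 = 1.50 | 22/16 = 1.38 |
| Infants | 14 | 24/14 = 1.71 | 22/14 = 1.57 |
| Children | 12 | 24/12 = 2.00 | 22/12 = 1.83 |

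The range is about 1.4 to 2.0.

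**Step 3: what this could do to a per-day count (illustration).** Assume that a day counts if it has at least one event, that detectable events arise at a constant hourly rate, that this rate is equal in the two arms, and that controls have a 24 h window. With control daily risk *p* and *h* intervention hours, the intervention arm shows 1 − (1 − *p*)^(*h*/24). The values of *p* are assumptions.

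| Control daily risk | Neonates (16 h) | Infants (14 h) | Children (12 h) |
|---|---|---|---|
| 10% | 6.8% | 6.0% | 5.1% |
| 20% | 13.8% | 12.2% | 10.6% |
| 30% | 21.2% | 18.8% | 16.3% |
| 50% | 37.0% | 33.3% | 29.3% |

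For example, 1 − 0.80^(12/24) = 0.106. The intervention arm looks safer in every cell although the hourly risk is the same. With a 22 h control window and *p* = 20%, replacing 24 by 22 in the exponent gives 15.0%, 13.2% and 11.5%.

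**Step 4: a true increase under the same assumptions.** Let the hourly rate in the intervention arm be 1.5 times that of controls, with *p* = 30%. The intervention arm shows 1 − 0.70^(1.5*h*/24): 30.0% in neonates, 26.8% in infants and 23.5% in children. A real increase would look like no difference in neonates and like benefit in the two older groups.

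**Step 5: after matching.** With the same clock window in both arms the ratio in Step 2 is 1.0, and the difference due to window length disappears.

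**The case against.** Four arguments weigh against the point.

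**The 24 h control window is an inference.** The control-group section describes how controls are fed, not how outcomes are counted. Because the article matches clock times for ketones and metabolism samples, the authors may intend the same here, and then there is no asymmetry. This stands as a limit: a reader might infer that the plan expressly counts control lactate around the clock, and it does not say so. But the words that fix the window, applied to patients fed around the clock, give 22 to 24 h, and nothing in the article says otherwise for this outcome.

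**The analysis plan for secondary outcomes is deferred to a separate publication.** Denominators and models may properly be left to it. The counting window is different, because the article states it. If the separate plan already matches clock hours, the published definition only needs to be aligned with it.

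**The size rests on unstated conditions.** A reader might infer that the intervention's hourly risk must be 1.5 to 2 times higher merely to look equal. That holds only for a per-day (or similar) count, a constant hourly rate, detection proportional to hours and a full 24 h control window. Lactate is seen only when arterial blood is drawn, and no lactate schedule is given. An elevation lasting many hours could be caught in either window. With per-sample counting, or equal sample numbers per arm, the bias would be small. This objection stands in full.

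**Another lactate analysis exists.** The course of lactate is a separate secondary outcome with no feeding-interval limit, and longitudinal metabolic markers go to mixed models. A reader might infer that harm would go unseen; this analysis makes that too strong. It does not repair the named safety comparison.

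**Conclusion.** The point holds in a limited form. As written, hyperlactatemia is tied to an interval whose length differs by arm, with no matched control window: 16, 14 or 12 h against 22 to 24 h, a ratio of about 1.4 to 2.0. If events are counted per patient or per day and lactate is sampled throughout the day, the comparison is biased toward the intervention. The direction follows from the text under those conditions. The percentages are illustrations on assumed risks and do not predict what the trial will show.

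The documents do not support saying that the trial will conceal harm. This is one of three secondary safety outcomes, below a separate primary safety outcome, and it bears on neither the primary end point nor the sample size. It should still be corrected before analysis, because the remedy is simple and the article already uses matched time points elsewhere.

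**What to change.** Amend the definition, and carry it into the separate analysis plan, as follows:

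1. Count arterial lactate above 2 mmol/L in both arms within the same age-stratum clock window: 10 AM to 2 AM for neonates, to 12 AM for infants and to 10 PM for children. Because the neonatal window crosses midnight, assign each window to the day on which it opens.
2. Report days with at least one event divided by intervention days, the same form as for hyperglycemia.
3. Show the number of arterial lactate samples per arm in that window, with a rate per sampled day or per sample as a sensitivity analysis.
4. Report all-hours hyperlactatemia in both arms as supportive.

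The cost is small. No new samples are needed, and the primary end point and sample size do not change. The change needs the clock time of each lactate value. The article says that routine chemistry is registered in the electronic patient file for later retrieval; that lactate is included there with its sampling time is a reasonable assumption, not something stated.

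Two downsides remain. Control values taken at night leave the main comparison, which is why the all-hours result is kept as supportive. Unless a lactate schedule exists elsewhere, sampling stays clinician-driven in a trial whose treating staff are unblinded, so a denominator limited to sampled days could select differently by arm. For that reason it belongs in the sensitivity analysis, with sample counts shown beside the main result.
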